### Recruitment

With support from clinical investigators, a Community Coordinator (CC) introduces the study to clinic staff at prospective recruitment sites and obtains permission to enroll from the facility head prior to beginning recruitment. The study asks clinic staff to approach all eligible women living with HIV registered for antenatal care, provide them with study information, and obtain their assent to be contacted by study staff.

Study staff visit the clinics weekly to obtain potential participant lists and contact them to confirm their eligibility, explain the purpose and procedures, and subsequently obtain informed consent for all study activities. Specifically, the CC meets with antenatal care (ANC) staff to arrange access to the ANC Register and to support identification of pregnant women meeting the eligibility criteria. Upon identification of potentially eligible women, the CC arranges for the health care worker to obtain assent to contact the mother directly. The CC begins direct engagement by reconfirming eligibility criteria are met—including the date of positive HIV test—prior to acquiring consent. With consent obtained, the study staff then completes the baseline assessment and discloses allocation to MME or TAU to the participant. Since this study focuses on the testing of intervention efficacy in a new context, we focus on recruiting into the MME group, and participants are placed into the control group based on overflow and availability (3:1). This also helps promote participant retention in the study.

Once the CC has identified a sufficient number of MME-allocated subjects within a cluster, study staff poll those participants to determine the week day suitable for the largest number of participants allocated to MME; the CC then makes a follow-up call to inform MME-assigned participants of the location, starting date, and anticipated end date of the group sessions. Sessions are scheduled to run at least once per week and may be scheduled twice per week if participants prefer, in order to maximize the possibility that all attendees benefit from all sessions of the intervention prior to delivery.

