### Condition assignment and blinding

Due to pragmatic challenges of recruiting pregnant women during the first 28 weeks of pregnancy, we are not able to use randomization. Participants who meet eligibility criteria are assigned by the research team to receive MME or TAU based on timing of recruitment (Fig. 2). Since we are not able to standardize the start of the intervention to the same week of pregnancy for participants, women are enrolled as long as it is feasible for them to complete eight sessions prior to week 36 of their pregnancy. In terms of blinding, participants and study staff administering the intervention are aware of treatment allocation; lead and senior investigators are blinded to treatment allocation. The biostatistician is not involved in the intervention assignment and is unblinded at the phase of analysis because the intervention group has measures immediately post-intervention that are not administered to the control group. Additionally, one of the primary analyses is to compare outcomes in the intervention group vs. the control group.

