### Data management

As part of capacity building, the data center is located at the University of Botswana. All data is collected and entered by trained research staff to be stored virtually on the University of Pennsylvania (UPenn) instance of REDCap. All assessments are recorded on the final version of the case reporting forms (CRFs) and inputted into the secure web-based data management system operated by the Data Management Unit (DMU) of the University of Botswana.

During data collection, security of the web-based data entry system is maintained through the use of a double authentication system. Each system user is assigned two username/password combinations. The first username/password combination is one selected by the registered user and provides access to the main data management website. Access to the website is limited to authorized users by the following condition: (1) all users must become registered with the DMU and (2) access to the DMU website will be restricted to study personnel who work with the UPenn instance of REDCAP and must be approved by the Director of DMU. The second username and password are assigned by the DMU and provides access to the data entry portion of the website. Strict standards are enforced when providing access to the data entry system. A co-investigator validates users in writing for access and security assignment. Additionally, all users of the web data entry system are required to complete CITI training and certification. The data center is unblinded and will adhere to the Data Safety and Monitoring Plan (DSMP), which informs reports, database locking, and analysis. A Data Safety and Monitoring Board (DSMB) will meet every 6 months to monitor adverse events (AEs) and safety outcomes. The DSMB consists of 3 experienced, doctoral-level HIV researchers (> 5 years of research in the field) who will meet every 6 months to review any adverse events and safety outcomes, and independently determine whether study activities will (1) continue as planned or (2) stop pending full IRB review and only continue pending subsequent IRB approval. Study personnel will abide by the determination of the DSMB.

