In regard to adverse events, we anticipate two events that may occur, intimate partner violence, and depression and suicidal ideation. In order to protect the privacy of participants and to mitigate the possibility of intimate partner violence, protections for participant privacy will include the following: contact only with the participant; no study-related information will be left on answering machines or other devices; no study-related information will be left with individuals who reside within the household. These procedures will also be followed when participants are contacted about the longitudinal evaluation at 16-week follow-up. When an instance of intimate partner violence is disclosed either during an anti-stigma group session or during the baseline or follow-up evaluation, the study team member who identified the event will report the date, description of the event, duration, severity, measures used to ameliorate effects of the event, and type of referral. The Project Director (AHO) will be notified immediately, and the report form will be reviewed and signed by the PIs (LHY and MB) within 24 h who will be responsible for ensuring that appropriate actions have been taken. The participant will be immediately referred to psychiatric counseling by a clinician under the supervision of our expert in-country psychiatrist Consultant (PO) and other supportive services (e.g., domestic violence support group). The clinician will conduct an in-person clinical evaluation within 24 h, and if the participant is found to be experiencing significant psychiatric distress, this clinician will immediately connect the participant with clinical services in the Princess Marina Hospital Department of Psychiatry, which will address any distress via in-person outpatient meetings and continuing therapy sessions as needed.

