Data analysis will be conducted by the biostatistician (MG). As part of an annual data audit, a clinical research compliance assessment will take place within 90 days of the IRB approval expiration date to assess the prior year’s activity. This is done by the UPenn in-country regulatory staff that are independent from the study team. This audit uses UPenn compliance tools that include a plan for reassessment if there are any issues that need to be addressed; the Research Director for the Botswana-UPenn Partnership will sign off on this process. The results are shared with the study team and all documentation will be completed by the Principal Investigator (LHY) and study staff. In addition, and in regard to data completeness and quality, we are conducting preliminary analyses in order to examine the data in real time and also utilize REDCap data completeness checks. The Principal Investigator (LHY) will also have access to these analyses. Should the trial need to be terminated, the Principal Investigator is responsible to make the final decision to terminate the trial.

All hard copy data are kept in locked filing cabinets in a locked office at all times. All data, including viral load and CD4 counts, are kept according to study participant number (de-identified). De-identified data including all paper interviews are kept separate from confidential data, such as contact information. Data is entered at University of Botswana situated offices and is subsequently stored at the Botswana-UPenn office. All data, once returned to the BUP study offices, are not be permitted to be removed. After data cleaning and analysis activities have concluded, all identifiable data, including patient locator forms, will be destroyed.

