Currently, little is known about how to reduce HIV stigma that interferes with postpartum treatment in a context of free antenatal care and ART treatment. This study offers a model for how to use formative research and the WMM theoretical framework to identify culturally meaningful aspects of stigma and adapt evidence-based stigma reduction intervention components for women living with HIV in Botswana. While we realize that changing stigma in other stakeholders (e.g., family, community members, healthcare providers) is crucial, here we choose to alleviate stigma among pregnant women living with HIV whom we have identified as having particular vulnerabilities towards stigma, in part due to inadvertent effects of current HIV treatment policies. The intervention explicitly focuses on this by helping women resist stigma that threatens their moral standing in the community and emphasizes how continued ART during postpartum contributes to being a good mother. By training peer co-leaders, we build on existing resources and enhance local capacity. We envision a cohort of local trainers with the ability to sustain the work and continue to reach women after the study ends. Finally, we are conducting a rigorous evaluation of the intervention. To our knowledge, this is one of the first studies to systematically evaluate a stigma reduction intervention using a peer contact-based approach in sub-Saharan Africa [35], and has the potential to be one of the only stigma interventions to show stigma-reducing effects into the postpartum period. We use the most robust pragmatic study design that is feasible in terms of recruitment and implementation. Although we lack randomization, we include a control group, systematically allocate to intervention or control, blind all research staff except those administering the intervention, conduct assessments at multiple time points, include both subjective and objective measures of health and wellbeing, and consider potential intergenerational effects with both mother and infant outcomes. We also track process outcomes including fidelity and dosage. Together, this will help inform further refinement of the MME intervention and preparation for a large-scale, multisite, randomized controlled trial in the future.

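### The claim that all staff not delivering MME are blinded is contradicted by the protocol's own procedures, and the stated blinding of lead investigators is not safeguarded

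*Protocol article*

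**What the plan says.** Blinding is described in two places in the protocol article, and the two differ in scope.

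- **Condition assignment and blinding** makes a limited statement. Participants and the staff delivering the intervention know the allocation; "lead and senior investigators are blinded to treatment allocation", with no end point or exception; and the biostatistician "is unblinded at the phase of analysis because the intervention group has measures immediately post-intervention that are not administered to the control group". Women are "assigned by the research team to receive MME or TAU based on timing of recruitment".
- **Discussion** goes further. Among the features set against the absence of randomisation, it says the study will "blind all research staff except those administering the intervention".

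Other sections describe who handles what:

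- **Recruitment**: after consent, "the study staff then completes the baseline assessment and discloses allocation to MME or TAU to the participant".
- **Data management**: "The data center is unblinded and will adhere to the Data Safety and Monitoring Plan (DSMP"). The same section routes safety reports to the PIs for review and signature within 24 hours. It also states, on data completeness and quality, that "we are conducting preliminary analyses in order to examine the data in real time", and gives the Principal Investigator access to those analyses.
- **Table 1 and Intervention process measures**: open-ended questions are put to MME women only, at all three time points. At baseline they concern hopes for the intervention; at 16 weeks they concern continued contact with group members and leaders.

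**The concern.** Allocation is neither random nor concealed from the team, so a reader will look for other safeguards, and the Discussion offers staff blinding as one of them. If the people who assign, assess, hold the data and analyse know the arm, that safeguard cannot be credited.

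Two things are at stake. First, stigma and psychosocial outcomes are self-reported to study staff, and the ART adherence instrument is a questionnaire. An interviewer who knows the arm can add to whatever bias the participant brings. Second, a Principal Investigator who is described as blinded but can look at accruing data may learn allocations without the protocol recognising it.

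**Working it through.** No arithmetic applies. The check is to compare each blinding statement with the procedures described for the people it covers.

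**A. The Discussion claim (all staff except those administering MME)**

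1. *Data centre.* Data management says outright that it is unblinded. This contradicts the claim.
2. *Biostatistician.* Condition assignment and blinding says this person is unblinded at analysis. This contradicts the claim from that point on.
3. *Staff who assign.* The research team allocates women by timing of recruitment. Whoever allocates knows the arm.
4. *Staff who recruit and assess at baseline.* They disclose the allocation, so they know it. Table 1 gives the baseline open-ended item to MME women only, so whoever asks it knows the arm by that point in the interview. The Community Coordinator, whose described duties are recruitment and scheduling, also identifies the MME-allocated women and telephones them about sessions.
5. *Whoever interviews at 16 weeks.* The protocol does not name this person. The MME-only questions would reveal the arm to anyone who asks them.

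Items 1 and 2 are express statements; items 3 and 4 follow from described duties; item 5 follows from the interview content. Counting recruiters and assessors as staff who administer the intervention would remove items 3 to 5, but items 1 and 2 would still contradict the claim.

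**B. The claim about lead and senior investigators**

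1. *Event reports.* Reporting applies "When an instance of intimate partner violence is disclosed either during an anti-stigma group session or during the baseline or follow-up evaluation", and depression or suicidal ideation follows the same pathway. Only MME women attend group sessions. A report of an event disclosed in a session therefore identifies an MME woman. A report arising from a baseline or follow-up evaluation can come from either arm, and the listed report contents do not include the arm. The leak is participant by participant.
2. *Real-time analyses.* The protocol's own reason for unblinding the biostatistician is that post-intervention measures exist only in the MME arm. The same structure would reveal the arm to anyone shown individual records or completeness by visit. The protocol does not say whether the Principal Investigator sees such output, pooled output or output by arm, and it describes no masking.

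The result for B is a stated protection with two open routes around it and no described barrier on either.

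**The case against.** The strongest reply is that the fault is one clause in the Discussion. The Methods section on blinding makes only the narrower claim and openly discloses the biostatistician's position; Data management openly discloses the data centre's. On this view little is hidden and only the Discussion sentence needs correcting. That is largely right about where the false statement sits. It does not remove the contradiction, because the Discussion presents the clause as a strength of the design.

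A reader might go further and infer that the lead investigators are not blinded at all. The documents do not support that. Event reports reveal the arm only when the event arose in a session. The preliminary analyses are tied to completeness and quality and are not said to be by arm. The Data Safety and Monitoring Plan, which is not shown, may contain masking rules.

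Three other inferences should also be resisted:

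- *That real-time access exposes accruing viral load results.* CD4 count and viral load are collected only once, at the end of the study.
- *That the Principal Investigator alone controls stopping.* The Principal Investigator is given the final termination decision, but a three-member DSMB independently determines whether activities continue, and study personnel abide by its determination.
- *That every outcome is assessed unblinded.* Birth and infant outcomes come from records, and nothing shows that those extracting them know the arm.

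It is also true that participants know their arm. Blinding staff could never have removed bias in self-reported outcomes, so the practical gain from better staff blinding is limited.

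**Conclusion.** The point holds in two parts of different strength. The statement that all research staff except those administering MME are blinded is wrong as written: two roles contradict it by express statement, and the assigning and assessing staff by their described duties. The blinding of lead and senior investigators is not safeguarded; it is not shown to be absent.

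No estimate, power figure or error rate changes, and the size of any resulting bias cannot be derived from the document. The consequence is that a non-randomised comparison is credited with a protection it largely lacks. This should be corrected, and correction is cheap.

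The conclusion assumes that the 16-week interviewer also asks the MME-only questions and that no masking of the Principal Investigator's interim output is set out in documents not shown. If either assumption fails, the corresponding part of the concern weakens; the contradiction over the data centre and the biostatistician stands.

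**What to change.** 1. Withdraw the all-staff claim in the Discussion. Reconcile it with Recruitment, Condition assignment and blinding, Intervention process measures and Data management by stating, role by role, who is blinded and until when.
2. Describe the interviewer-collected self-report outcomes as not blinded. Leave record-extracted outcomes out of that description unless the extractors know the arm.
3. Limit the interim output available to the Principal Investigator to pooled completeness and quality counts, without arm, post-MME or attendance fields. Confine by-arm data to the data centre, the biostatistician at analysis and the DSMB.
4. At 16 weeks, complete the self-report scales before asking the MME-only qualitative questions.
5. State that PI review of event reports, which stays unchanged, can unblind the PIs for individual participants.

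The cost is some rewording, a restriction on data exports and a fixed order for the 16-week interview. A claimed strength will be stated less favourably.

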### Trial status

As of submission, this protocol is version 2 and is registered with Clinical Trials, www.clinicaltrials.gov, (NCT03698981) as of October 8, 2018. Recruitment began in March 15, 2019, and will be completed as of October 31, 2020.

## Data Availability

Access to a de-identified dataset will be made available upon reasonable request following primary manuscript publication. The Principal Investigator ([name], [contact]) can be contacted for details.

## Abbreviations

MME: “Mothers Moving towards Empowerment”
TAU: Treatment as usual
WMM: What matters most
ART: Antiretroviral therapy
HIV/AIDS: Human immunodeficiency virus infection/acquired immune deficiency syndrome
CD4 count: Cluster of differentiation 4
MTCT: Mother-to-child transmission
PMTCT: Prevention of mother-to-child transmission
PLWHA: Person living with HIV/AIDS
RCT: Randomized controlled trial
MOH: Ministry of Health
IDCC: Infectious Disease Care Clinic
GGDHMT: Greater Gaborone District Health Management Team
ANC: Antenatal care
DSMB: Data Safety and Monitoring Board
DMU: Data Management Unit
CRFs: Case reporting forms
CC: Community Coordinator
CBT: Cognitive behavioral therapy
BUP: Botswana Upenn Partnership (BUP)
APGAR Score: Appearance, Pulse, Grimace, Activity, and Respiration
PROMIS: Patient-Reported Outcomes Measurement Information System
WHODAS 2.0: World Health Organization Disability Assessment Schedule 2.0
QOL Scale: Quality of Life Scale
CES-D: Center for Epidemiological Studies Depression Scale
PCL-5: Post-Traumatic Checklist for DSM-5
ACTG: AIDS Clinical Trial Group
IPV–WAST: Intimate Partner Violence – Women Abuse Screening Tool
GEE: Generalized estimating equations
SEM: Structural equation models
PASS 2019: Power Analysis and Sample Size Software 2019
PI: Principal Investigator
